### Participants

Among the depressed patients who visit the medical facility in this study, those who meet all the inclusion criteria of the patient group (escitalopram, usual care, and cross-sectional study groups) and do not meet any of the exclusion criteria of the patient group will be included in the patient group.

The inclusion criteria for the patient group will be as follows: (1) men and women whose age during consent is between 20 and 75 years, (2) patients diagnosed with MDD following the Mini International Neuropsychiatric Interview (MINI) [9] measured after obtaining consent, and (3) voluntary written consent to participate in this study.

The exclusion criteria of the patient group will be: (1) patients with a mental state in which it is difficult to understand the purpose of the study, (2) patients with MDD with psychotic features, (3) diagnosed with bipolar disorder or schizophrenia, (4) diagnosed with substance abuse within 6 months before obtaining consent, (5) treatment for anxiety disorders within 6 months before obtaining consent, (6) personality disorder coexisting during consent, (7) patients with a marked suicide tendency, (8) patients with MRI contraindications, and (9) patients judged by the principal investigator or the co-investigator to be inappropriate as a research participant.

The HCs will be recruited from local communities. The inclusion criteria of HCs will be (1) men and women aged between 20 and 75 years during consent, (2) persons without any mental illness following MINI measured after obtaining consent, and (3) persons who have voluntarily consented to participate in this study in writing. The exclusion criteria of the HCs will be (1) persons with or with a history of mental or neurological disorders, (2) persons with MRI contraindications, and (3) persons judged by the principal investigator or co-investigator to be inappropriate as a research participant.

### Allocation

Patients with MDD who consent to participate in this study will be assigned to either the escitalopram group, usual care group, or cross-sectional study group based on the following criteria during enrollment. The applicability of each group will be confirmed in the following order: escitalopram group, usual care group, and cross-sectional study group.

The inclusion criteria for the escitalopram group will be as follows: (1) no treatment or less than 2 weeks of antidepressant treatment with an escitalopram-equivalent dose of 5 mg/day or less during the current depressive episode, and (2) patients who are suitable to start treatment with escitalopram based on the clinical judgment of a physician.

The exclusion criteria of the escitalopram group will be as follows: (1) use of mood stabilizers and antipsychotics; (2) receiving electroconvulsive therapy within 3 months before informed consent; (3) receiving standardized psychotherapy (including cognitive-behavioral therapy and interpersonal therapy) other than standard outpatient psychotherapy; and (4) contraindications for escitalopram.

The inclusion criteria of the usual care group will be as follows: (1) no treatment or less than 2 weeks of antidepressant treatment with an escitalopram-equivalent dose of 5 mg/day or less during the current depressive episode; (2) not meeting the inclusion criteria for the escitalopram group or inability to continue escitalopram treatment for 6 weeks.

The exclusion criteria for the usual care group will be as follows: (1) use of mood stabilizers and antipsychotics; (2) receiving electroconvulsive therapy within 3 months before informed consent; and (3) receiving standardized psychotherapy other than standard outpatient psychotherapy.

Regarding the cross-sectional study group, among the patients who meet the participation criteria for this study, those who do not meet the selection criteria for either the escitalopram group or the usual care group are eligible.

### The target number of participants and the basis for setting

The target number of participants in each group is as follows:

Escitalopram group: 80 participants.Usual care group: 60 participants.Cross-sectional study group: 200 participants.HCs: 50 participants.

The number of cases required for the main examination in this study was calculated as follows:

The number of participants required to verify that patients with MDD and HCs can be distinguished using a “diagnostic marker” was set based on the following criteria. The AUC was approximately 0.77 in the data of our previous study. [6] Assuming that the AUC is 0.65 conservatively and calculating the sample size (http://www.biosoft.hacettepe.edu.tr/easyROC/) that can detect AUC > 0.5 with Type, I error: 0.05 and power: 0.8, 43 participants will be required for each group. Assuming a 10% chance of cancellation or dropout, it was considered appropriate to aim for 50 registrations per group.The reasons for setting the number of cases required to verify whether the rate of symptom improvement among the MDD subtypes identified by the stratification markers in the escitalopram group differed significantly are as follows. Based on a power analysis for the Mann–Whitney U test using the method developed by Shieh et al. [10], the sample size calculation was performed with Type I error 0.05, power: 0.8 using R’s shiehpow function (https://www.rdocumentation.org/packages/wmwpow/versions/0.1.3/topics/shiehpow). Therefore, 68 participants will be required. Predicting approximately 10% cancellation or dropout, it was considered appropriate to aim for the registration of 80 participants.Based on past medical records, approximately 60 and 200 patients are expected to be eligible for the usual care group and cross-sectional study group within the registration period, respectively. The data obtained from the escitalopram and usual care groups will be used to determine whether the “brain network marker of MDD diagnosis” reflects the therapeutic effects in patients with depression (Purpose 2). In addition, we will conduct exploratory investigations to determine whether there is a significant difference in the rate of symptom improvement between subtypes by “stratification markers” in the data of the usual care group combined with the data that XNef, Inc. possesses (Purpose 4). Furthermore, the MRI data obtained from all groups will be used as training data to improve the accuracy of the AI program that assists in diagnosing MDD (Purpose 5). Based on these findings, obtaining as much data as possible from eligible patients in non-interventional groups is desirable. Therefore, although it is difficult to imagine a situation where the expected number of cases is significantly exceeded in reality, if the expected number of cases is exceeded, all patients who have provided consent within the registration period should be allowed to be enrolled.

### MRI acquisition

MRI scans will be obtained for all participants using a 3.0 Tesla MRI system (Siemens MAGNETOM Skyrafit; Siemens, Erlangen, Germany) at Hiroshima University. Additionally, rs-fMRI scans will be acquired for 10 min from each participant using the following scanning parameters: slice number, 40; matrix size, 64 × 64; FOV, 212 mm; voxel size, 3.3 × 3.3 × 3.2 mm (slice gap, 0.8 mm); TR, 2,500 ms; TE, 30 ms; flip angle, 80°. T1-weighted structural images will also be acquired using the following scanning parameters: matrix size, 320 × 300 × 224; FOV, 256 × 240 × 179.2 mm; voxel size, 0.8 × 0.8 × 0.8 mm.

### Preprocessing and calculation of the resting-state FC matrix

The preprocessing and calculation of the resting-state FC matrix have been described in detail elsewhere. [6] We will preprocess the rs-fMRI data using FMRIPREP version 1.3.2. [11] The first 10 s of the data will be discarded to allow T1 equilibration. The preprocessing steps include slice-timing correction, realignment, coregistration, distortion correction using a field map, segmentation of T1-weighted structural images, normalization to the Montreal Neurological Institute space, and spatial smoothing with an isotropic Gaussian kernel of 6 mm full-width at half maximum. To analyze the data, we will use the ciftify toolbox version 2.3.2. [12] We will use Glasser’s 379 surface-based parcellations (cortical 360 parcellations + subcortical 19 parcellations) as regions of interest (ROIs); [13] the blood oxygen level-dependent (BOLD) signal time courses will be extracted from these 379 ROIs. A temporal bandpass filter will be applied to the time series using a first-order Butterworth filter with a pass band between 0.01 and 0.08 Hz. Framewise displacement will be calculated for each functional session, and we will remove volumes with a framewise displacement > 0.5 mm along with the previous and two subsequent volumes. [14] If the ratio of the excluded volumes after scrubbing exceeds 47%, the participants will be excluded from the primary analysis. [6] FC will be calculated as the temporal correlation of rs-fMRI BOLD signals across 379 ROIs for each participant. Fisher’s *z*-transformed Pearson’s correlation coefficients will be calculated between the preprocessed BOLD signal time courses of each possible pair of ROIs and used to construct 379 × 379 symmetrical connectivity matrices. We will use 71,631 FC values ([379 × 378] / 2) of the lower triangular matrix of the connectivity matrix for further analysis.

### Analysis of the primary endpoint

As 100 classifiers of MDD (tenfold cross-validation × 10 subsamples) were created in the original study [6], we will apply all of these classifiers to the new dataset and average the 100 outputs (depression probability value) for each participant.

A ROC curve will be estimated for discrimination between HCs and patient groups (regardless of the escitalopram group, usual care group, or cross-sectional study group, the 50th or less in the order of registration will be analyzed) based on the depression probability value. We will display the (sensitivity, 1-specificity) coordinate position corresponding to the optimal cutoff value based on the Youden index, along with point estimates of AUC, optimal cutoff value, sensitivity, and specificity. For AUC, if a 90% confidence interval is constructed and the lower endpoint of the confidence interval is ˃ 0.5, it will be interpreted as AUC > 0.5, with a type I error of 5%.

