**Methods:**

This is a non-randomized, open-label study involving patients with MDD and healthy controls (HCs). We will prospectively acquire rs-fMRI data from 50 patients with MDD and 50 HCs and anterogradely verify whether our diagnostic marker can distinguish between patients with MDD and HCs. Furthermore, we will longitudinally obtain rs-fMRI and clinical data at baseline and 6 weeks later in 80 patients with MDD treated with escitalopram and verify whether it is possible to prospectively distinguish MDD subtypes that are expected to be effectively responsive to escitalopram using our stratification markers.

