Although many studies have reported the biological basis of psychiatric disorders, none have been put into practical use or are useful in clinical practice. Particularly, resting-state functional magnetic resonance imaging (rs-fMRI) is expected to be put into practical use owing to its safety and provision of a large amount of information. However, there is a great difficulty in practical use because the nature of the data differs depending on the measurement facility. Therefore, we integrated rs-fMRI data acquired at multiple institutions by the harmonization method using traveling individuals as homogeneous large-scale data (total of 1,584 cases) [5] and subsequently applied a cutting-edge machine learning method to develop a brain network marker for MDD diagnosis [6]. This brain network marker can distinguish between healthy individuals and patients with MDD with a probability of approximately 70%, even for completely independent data obtained at different facilities [6]. Therefore, we designed this study as a clinical trial to establish anterograde evidence for the practical application of this brain network marker for MDD diagnosis (diagnostic marker) as Software as a Medical Device. In addition, we developed brain network markers for MDD stratification (stratification marker) with robustness among independent datasets by performing unsupervised machine learning on rs-fMRI data of patients with MDD [7]. Statistically significant differences were also observed in the therapeutic responsiveness to escitalopram between the MDD subtypes discriminated by these brain network markers. Therefore, the anterograde verification of these stratification markers was set as the secondary endpoint of this study. The results of this study will provide useful information for the diagnosis and treatment selection of MDD using rs-fMRI.

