## Discussion

Given fMRI can non-invasively evaluate changes in brain activity with a high spatial and temporal resolution, it has been applied to research on psychiatric disorders, and many results have been reported. For clinical applications, rs-fMRI is attracting attention as a method that can evaluate brain activity without frequently difficult tasks in patients with cognitive and motivational deficits. Initially, analyses were performed to detect statistically significant differences by comparing patients and HCs; however, recently, machine learning methods aimed at discrimination at the individual level have been used. Meta-analyses [15, 16] of such studies have shown good discriminative results, raising expectations for clinical applications. However, it has been highlighted that when commonly used machine learning methods are applied to a small data sample of dozens of individuals, overfitting causes inflation in leave-one-out cross-validation discriminant results, resulting in poor generalization performance to independent external data [17]. Our diagnostic marker [6], which was developed by integrating fMRI data acquired at different facilities as large-scale data by harmonization using traveling individuals [5], has a generalization performance to multiple external independent data with an accuracy of approximately 70%. Therefore, it is considered suitable for prospective clinical research aimed at practical applications. In this study, we will confirm that sufficient accuracy of the diagnostic marker [6] could be reproduced for data from a prospective clinical study.

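### Sensitivity and specificity will be reported at a Youden cutoff chosen on the trial's own participants, which overstates them; the primary AUC analysis is not affected

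*Protocol article*

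**What the plan says.** Analysis of the primary endpoint takes the 100 classifiers built in the development study and says "we will apply all of these classifiers to the new dataset and average the 100 outputs (depression probability value) for each participant". The marker itself is thus fixed. The next step is new estimation: "A ROC curve will be estimated for discrimination between HCs and patient groups", with the patient side limited so that "the 50th or less in the order of registration will be analyzed". From that curve the plan displays the point "corresponding to the optimal cutoff value based on the Youden index, along with point estimates of AUC, optimal cutoff value, sensitivity, and specificity". The cutoff is listed among the quantities to be estimated. The only confidence interval described is the 90% interval for the AUC.

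The planned size is given in the abstract: "We will prospectively acquire rs-fMRI data from 50 patients with MDD and 50 HCs". Dropout, and the rule excluding participants with more than 47% of volumes scrubbed, can make the analysed number smaller.

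On purpose, the Discussion says "we will confirm that sufficient accuracy of the diagnostic marker" can be reproduced prospectively. The Background states that the marker separates patients from healthy individuals "with a probability of approximately 70%, even for completely independent data obtained at different facilities".

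**The concern.** A validation study of a fixed marker should carry the decision threshold over with the marker. Here the classifiers are fixed but the threshold is re-estimated on the validation sample, and sensitivity and specificity are read off at the point where their sum happens to be largest in that sample. Such a maximum is optimistic on average, even for a marker with no information.

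Sensitivity and specificity are the figures that a user of a diagnostic device would rely on, and the article describes the trial as evidence for Software as a Medical Device. An accuracy claim needs a threshold. If the threshold is tuned on the trial data, an apparent reproduction of about 70% is partly produced by the tuning.

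A related point is a shift of the probability scale on the trial's single scanner. The AUC and the Youden sensitivity and specificity do not change when all scores move together. The shift would show only through the estimated cutoff, which is imprecise at this sample size.

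**Working it through.** **Inputs from the article.** 50 per group planned; AUC about 0.77 in the earlier study; planning AUC 0.65 against 0.5; type I error 0.05, power 0.8, 43 per group; 10% dropout.

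**Assumption, not in the article.** Scores are normal with unit variance in both groups, means 0 and δ, with δ = √2·Φ⁻¹(AUC). AUC 0.50 and 0.70 are added to show the range.

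**The plan's own figure.** With the binormal variance V(A) = 0.0099·exp(−a²/2)·[(5a² + 8) + (a² + 8)], a = 1.414·Φ⁻¹(A):
- V(0.5) = 0.0099 × 16 = 0.1584; V(0.65) = 0.1518 (a = 0.545).
- n = (1.645·√0.1584 + 0.842·√0.1518)² / 0.15² = 42.9, so 43 per group, as stated, with a one-sided 5% level. This agrees with the 90% interval rule. (A two-sided level would give 55.)
- 43/0.9 = 47.8, so 48, rounded up to 50 in the article.

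This calculation contains no cutoff, so the point below does not touch it.

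**Why the direction is certain.** Let J = sensitivity + specificity − 1. In any sample, the largest empirical J is at least the empirical J at any one fixed cutoff, including the truly best one. At a fixed cutoff the empirical J is unbiased. So the mean of the reported maximum is at least the true best J, which in turn is at least the true J at whatever cutoff the sample selected. No distribution is assumed.

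**Size.** The true best value is J = 2Φ(δ/2) − 1. At AUC 0.65, δ = 0.545 and J = 2 × 0.607 − 1 = 0.215. At AUC 0.77, δ = 1.045 and J = 2 × 0.699 − 1 = 0.399. In 20,000 simulated trials of 50 + 50 for each AUC, the cutoff was chosen to maximise J in the sample and then evaluated in the population. Balanced accuracy is (1 + J)/2; with equal groups it equals overall accuracy.

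| True AUC | Mean J reported | Mean true J at that cutoff | Balanced accuracy reported | Achieved in new patients | Best fixed cutoff |
|---|---|---|---|---|---|
| 0.50 | 0.116 | 0.000 | 55.8% | 50.0% | 50.0% |
| 0.65 | 0.292 | 0.195 | 64.6% | 59.7% | 60.7% |
| 0.70 | 0.362 | 0.269 | 68.1% | 63.5% | 64.5% |
| 0.77 | 0.461 | 0.378 | 73.1% | 68.9% | 69.9% |

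- Reported minus achieved, on sensitivity plus specificity: 0.292 − 0.195 = 0.097 at AUC 0.65 and 0.461 − 0.378 = 0.083 at AUC 0.77. Half of each gives 4.9 and 4.2 points of balanced accuracy (4.1 from unrounded values at 0.77).
- Reported minus best fixed cutoff: 64.6 − 60.7 = 3.9 points and 73.1 − 69.9 = 3.2 points (3.1 unrounded).
- A cutoff fixed in advance is unbiased: mean J 0.213 against a true 0.215 at AUC 0.65.
- With 43 per group at AUC 0.65 the overstatement rises to 0.301 − 0.193 = 0.108.
- The standard deviation of the selected cutoff is 0.35 score SDs at AUC 0.77 and 0.47 at AUC 0.65.

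**What it could do to the 70% comparison.** If the true AUC were 0.70, the Youden rule would show balanced accuracy of 70% or more in roughly 36% of trials. At the best fixed cutoff, the standard error is √(2 × 0.645 × 0.355/50)/2 = 0.048, and (0.700 − 0.645)/0.048 = 1.15, so the corresponding chance is about 1 in 8.

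**Scale shift.** In the same model at AUC 0.77, moving all scores up by 0.5 SD changes a fixed midpoint cutoff from 70% sensitivity and 70% specificity to Φ(1.022) = 85% and Φ(0.022) = 51%. The AUC and the Youden sensitivity and specificity stay the same; only the estimated cutoff moves, by 0.5 SD against its own standard deviation of 0.35.

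**The case against.** The strongest reply is that no endpoint or decision rests on the cutoff. The primary endpoint is the AUC, the only success rule is its lower 90% limit above 0.5, and sensitivity and specificity are not among the secondary endpoints. The Youden point is displayed as a description, with no target attached. This stands, and it limits the severity.

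Four stronger readings are tempting, and the article does not support them:
- *That the primary result is compromised.* It is not: the AUC needs no cutoff.
- *That nobody fixed a cutoff in advance.* The full protocol, any analysis plan and the development study are not shown. What can be said is that the one rule stated in the article is chosen in-sample.
- *That the results cannot be compared with the earlier 70%.* The article does not say which cutoff or accuracy measure produced that figure. Optimism weakens the comparison but does not rule it out.
- *That a scale shift would be hidden.* The estimated cutoff is itself reported, so a large shift could show there, although imprecisely.

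It is also fair that the size rests on a binormal model, whereas the trial's score is an average of 100 probability outputs. About 1 of the 5 points at AUC 0.65 is the loss from carrying a noisy cutoff to new patients (60.7 − 59.7), not inflation above the best attainable value. And the standard error of balanced accuracy at a fixed cutoff is √(2 × 0.607 × 0.393/50)/2 = 4.9 points at AUC 0.65, so the bias is at most about one standard error. A bias of that order in one direction still matters for a figure given as a point estimate.

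**Conclusion.** The concern holds as a moderate reporting problem. Followed as written, the plan overstates sensitivity and specificity, because the cutoff is selected and evaluated on the same participants and no correction is described. This is a rule that the article itself fixes, not a detail left open.

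The overstatement is about 4 to 5 points of balanced accuracy against performance in new patients, and about 3 to 4 points against the best fixed cutoff, for AUC 0.77 to 0.65 with 50 per group. It grows somewhat if fewer are analysed. These sizes assume equal-variance binormal scores; the upward direction of sensitivity plus specificity does not. What is at stake is the Discussion's aim of confirming accuracy, not the AUC test.

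**What to change.** Before any depression probability values from the trial are computed or linked to diagnosis, state the cutoff on the averaged depression probability that is carried over from the development study. The study is open-label, so the timing should be tied to that step and not to unblinding. Then:
- report sensitivity, specificity and accuracy at that cutoff, with 95% confidence intervals, as the main accuracy figures;
- keep the Youden point, labelled exploratory, with a bootstrap optimism correction;
- say which cutoff and accuracy measure lie behind the earlier figure of about 70%, so that like is compared with like.

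The cost is wording and one further line of analysis; recruitment, scanning and the primary test are unchanged. The downside is that the reported sensitivity and specificity will probably be somewhat less favourable.

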### Analysis of secondary endpoints

The patients will be grouped into remission and non-remission groups based on the severity of depression at 6 weeks and 6 months, using the escitalopram and usual care groups as the populations to be analyzed. The depression probability value will be analyzed for two factors using these data: remission/non-remission *treatment time point (0 w, 6 w, 6 m), and a test will be conducted at a significance level of 5%.

With escitalopram as the target group for analysis, patients with MDD will be stratified using stratification markers. The rate of symptom improvement evaluated using the HRSD will be compared between depression subtypes and tested at a significance level of 5%.

Patients with MDD in the usual care group combined with the data from XNef, Inc. will also be stratified using the stratification markers. The rate of symptom improvement evaluated using HRSD will be compared between depression subtypes and tested at a significance level of 5%.

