### Primary and secondary endpoints

The primary endpoint will be the area under the curve (AUC) of the receiver operating characteristic (ROC) curve when distinguishing between patients with MDD and HCs using the depression probability value calculated from the diagnostic marker at week 0.

The following will be the secondary endpoints:

Longitudinal evaluation of the diagnostic marker: The depression probability value, which is the output of the diagnostic marker, will be analyzed with two factors: remission/non-remission and time of treatment (0 w, 6 w, 6 m). Remission has been defined as a depression severity of 7 points or less using the Hamilton Rating Scale for Depression (HRSD).Depression severity will be obtained longitudinally (0 w, 6 w) in the escitalopram group; we will compare the rate of symptom improvement evaluated using the HRSD among the subtypes identified by the stratification markers in the escitalopram group.Depression severity will be obtained longitudinally (0 w, 6 w) in the usual care group, and we will compare the rate of symptom improvement evaluated using the HRSD among the subtypes identified by the stratification markers in the usual care group.

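### The usual-care subtype endpoint is defined in trial patients, but the only analysis described tests those patients pooled with company-held data, and its status differs between sections

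*Protocol article*

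**What the plan says.** Three sections of the protocol article describe this comparison.

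- **Primary and secondary endpoints.** Under the lead-in "The following will be the secondary endpoints", the third item states: "Depression severity will be obtained longitudinally (0 w, 6 w) in the usual care group". HRSD improvement is then compared "among the subtypes identified by the stratification markers in the usual care group". No outside data are mentioned.
- **Analysis of secondary endpoints.** The analysis population is wider: "Patients with MDD in the usual care group combined with the data from XNef, Inc. will also be stratified using the stratification markers". The comparison between subtypes is tested at 5%, the same level as the escitalopram comparison described just before it.
- **The target number of participants and the basis for setting.** Here the authors write that "we will conduct exploratory investigations to determine whether there is a significant difference in the rate of symptom improvement between subtypes", and place this "in the data of the usual care group combined with the data that XNef, Inc. possesses (Purpose 4"). The 60 usual-care patients are an expected count from past records. No effect size or power is given for this comparison.

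The Background adds a general statement that "the anterograde verification of these stratification markers was set as the secondary endpoint of this study". Under Purposes of the study, Purpose 4 (drug therapies other than escitalopram) is worded as something to be examined, while Purpose 3 (escitalopram) is to be verified.

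**The concern.** The endpoint is stated for one population and tested in another. Someone following the endpoint section would analyse the trial's usual-care patients. Someone following the analysis section would analyse those patients plus an unspecified set of cases the company already holds. Both cannot be reported as the result of the same endpoint, and the article describes only the second.

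This changes what can be concluded. A pooled p-value answers whether the subtypes differ in the mixture of trial and held patients. It does not answer whether they differ among the patients this trial enrols. If the held cases are numerous, or show a subtype difference of their own, the pooled test can be significant when the trial's usual-care patients show nothing.

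The label also moves, from a listed secondary endpoint with a 5% test to an exploratory investigation. A reader of the results would not know how much weight the comparison was meant to carry.

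**Working it through.** **Step 1: compare the sections.**

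| Section | Population | Status |
|---|---|---|
| Primary and secondary endpoints | usual care group | secondary endpoint |
| Target number of participants | usual care group plus held data | exploratory |
| Analysis of secondary endpoints | usual care group plus held data | tested at 5% under the secondary endpoints |

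The population in the first row has no analysis. The population in the other two rows has no matching endpoint.

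**Step 2: is there a figure in the plan to reproduce?** No. The usual-care number is an expected count of 60, with no effect size, standard deviation, subtype split or power.

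**Step 3: how far could held data drive the pooled result?** This is an illustration, not an estimate.

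Input from the article: 60 usual-care patients and a 5% level. Assumed: a two-sided test, two subtypes of equal size in both sources, unit standard deviation, a normal approximation, no subtype difference in the 60 trial patients, and a difference of δ SD in *m* held patients.

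- Total: N = 60 + m
- Pooled difference: d = δ × m / N
- Shift of the test statistic: s = d × √(N/4)
- Rejection probability: 1 − Φ(1.96 − s) + Φ(−1.96 − s)

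Example with δ = 0.3 and m = 60: N = 120; d = 0.3 × 60/120 = 0.15; s = 0.15 × √30 = 0.82; rejection = 1 − Φ(1.14) + Φ(−2.78) = 0.13.

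| δ in held data | m = 0 | m = 30 | m = 60 | m = 120 | m = 240 |
|---|---|---|---|---|---|
| 0.3 SD | 5% | 7.6% | 13% | 27% | 55% |
| 0.5 SD | 5% | 12% | 28% | 61% | 93% |
| 0.8 SD | 5% | 24% | 59% | 95% | about 100% |

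These are not false-positive rates for the pooled population, because a difference does exist in part of it. They show how often a significant pooled test would occur although the trial's own usual-care patients have no difference.

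**Step 4: what can the usual-care patients show alone?** With equal subtypes, a two-sided 5% test and 80% power, the detectable difference is (1.96 + 0.84) × 2/√N. For N = 60 this is about 0.72 SD. If 10% were lost, N = 54 and it is about 0.76 SD. The 10% is borrowed from the article's other two calculations; it is not stated for this group.

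**The case against.** The strongest reply is that the pooling is disclosed, tied to Purpose 4 and called exploratory, with no power claim. A secondary endpoint can be exploratory, and a nominal 5% level does not by itself make a test confirmatory. The article also condenses a fuller protocol, so the make-up of the held data and the handling of data source may be set out elsewhere. Much of this stands. The difference in status alone would be a minor point, and silence on those details is not a fault. What it does not answer is the population conflict: the printed endpoint and the printed analysis name different patients, and a fuller document cannot follow both.

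A reader might infer more, and the article does not support it:

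- *That a claimed prospective verification fails.* Purpose 4 is only to be examined, and the Background's statement on verification follows directly on a sentence about escitalopram response. The article does not call this particular test a verification.
- *That the test is circular.* Nothing says the held cases were used to build the markers. The markers came from unsupervised learning on imaging data, so on that description HRSD improvement was not a training target, and overlap alone would not make the response comparison circular.
- *That the 5% error rate is lost because held data will be picked after they are seen.* No such choice is described.
- *That most of the analysed patients will come from outside the trial.* The number of held cases is not given. A share of outside patients is also not in itself a bias or an error rate.

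**Conclusion.** The concern holds as a mismatch between endpoint and analysis. The third secondary endpoint is defined in the usual care group, the only described test is on that group pooled with company-held data, and the status of the comparison is not consistent. A significant pooled result need not reflect trial patients. Under the stated assumptions, with no effect in the 60 trial patients, the pooled test rejects between 7.6% of the time (0.3 SD, 30 held cases) and nearly always (0.8 SD, 240 held cases). The held-case counts and effects are assumed, so only the direction is firm.

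The reach is limited. The primary AUC analysis and the escitalopram subtype test draw on trial participants only and are untouched. This should be fixed, but it does not threaten the trial's main conclusion.

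**What to change.** 1. Test the third secondary endpoint in the trial's usual-care patients only, as the endpoint section defines it.
2. Report the pooled analysis separately, labelled exploratory as in the sample-size section, and stratified by or adjusted for data source.
3. Fix the held data set before any usual-care subtype outcome is examined. The study is open-label, so unblinding cannot serve as the cut-off. Exclude any case used to develop the markers, or show such cases separately.
4. State the same population and status in the endpoint, sample-size and analysis sections.

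The cost is modest but more than rewording: one additional analysis, a listing of the held data with any development cases identified, and lower precision for the usual-care-only test (about 0.72 SD detectable, as worked above). That precision is what the trial's own usual-care data can provide. The pooled data remain usable as supporting evidence.
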